### Subject

All subjects will be provided informed, written consents after the study procedure has been fully explained in detail. Females who match the following criteria would be included in the migraine group: (1) age ranges from 40 to 55 years old; (2) irregular menstrual cycle; (3) suffered from migraine; (4) normal neurological examination. Females who match the following criteria would be included in the HC group: (1) age ranges from 40 to 55 years old; (2) irregular menstrual cycle; (3) not suffered from any kinds of headache; (4) normal neurological examination. Exclusion criteria will be as follows: (1) severe psychiatric disorders, such as dementia, episode, epilepsy, major depression; (2) significant neurological illness, such as significant head trauma, tumor, meningitis or central nervous system (CNS) inflammatory lesions and vascular complications clues; (3) any MRI contraindications; (4) alcohol, nicotine or drug abuse.

Sample size have been estimated by referring to other studies [22, 23]. A sample size of 40 patients per group will be suitable for a power of 0.8 and an alpha significance level of 0.05 (two-side). Considering the drop-out ratio (25%) and unqualified images of included subjects, the total sample size is 55 in each group.

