### Statistical analysis

Statistical Package for the Social Sciences (SPSS) 18.0 (SPSS, Chicago, IL, USA) will be used to analyze the socio-demographic and clinical data. SPM8 and REST 1.8 will be used to analyze the imaging data. All statistical tests were conducted with a significance level of 5%.

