#### Functional and perfusion parameters

Both voxel-based and ROI-based 2-sample Student-t test will be applied to compare global ReHo, ALFF/fALFF, CBF between susceptible group and healthy control group with age, sex, education and BMI as covariance. The reference time series for headache-related seed regions will be acquired by averaging the time series for all voxels within them. Correlations of this time-series will be calculated to measure FCs among these regions in each participant. To evaluate group differences in the resting-state topological properties, nonparametric permutation tests were applied [29]. Initially, we will calculate the between-group differences of the mean values for each topological property. Next, an empirical distribution of the difference will be obtained by randomly reallocating every property value into two groups and recomputing the mean differences between the two randomized groups (5,000 permutations) to test the null hypothesis that the observed group differences only occurred by chance. The 95th percentile points of each distribution will be used as critical values for a two-tailed test to determine whether the observed group differences could occur by chance. Non-parametric Spearman correlation will also be performed to delineate a possible relationship between functional alterations and clinical data as well as perfusion alterations and clinical data. Significance threshold will be set at *P* < 0.05 (FWE corrected).

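### The cut-off stated for the two-tailed topology permutation test gives about 10% type I error if coded literally, not the stated 5%; the sentence should be corrected

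*Protocol article*

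**What the plan says.** The procedure is in the Protocol article, Statistical analysis, under Functional and perfusion parameters. It has four steps.

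- Method: "To evaluate group differences in the resting-state topological properties, nonparametric permutation tests were applied".
- Observed statistic: "we will calculate the between-group differences of the mean values for each topological property".
- Reference distribution: property values are reallocated at random to two groups, "recomputing the mean differences between the two randomized groups (5,000 permutations").
- Decision rule: "The 95th percentile points of each distribution will be used as critical values for a two-tailed test".

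The opening paragraph of Statistical analysis fixes the error rate: "All statistical tests were conducted with a significance level of 5" per cent. The Subject section is consistent with that level and with two-sided testing: "A sample size of 40 patients per group will be suitable for a power of 0.8 and an alpha significance level of 0.05 (two-side").

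Topological properties are listed under Secondary outcomes measure. The primary outcome is white matter integrity, and its tests are described under Structural parameters.

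**The concern.** A two-tailed test at 5% has to leave 2.5% in each tail of a signed reference distribution. The distribution described is that of the mean difference itself, and no step takes its absolute value. Its 95th percentile leaves 5% above it. A single percentile of a signed distribution therefore cannot serve as the critical value of a two-tailed 5% test.

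This is a matter of the tail area of each single test. It would remain with only one topological property, and it is separate from any correction across properties.

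At stake is whether a network measure is declared different between migraine and control groups. The Background intends significant group differences to serve as objective biomarkers, and the Correlation analysis section carries the most sensitive parameters into ROC curves. A cut-off that is too lenient would let more chance differences into that selection. If the sentence stays open, the choice of cut-off could also be made after the differences are known.

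**Working it through.** **Inputs**

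- Nominal level 5%, from Statistical analysis.
- Statistic: difference of group means, no absolute value stated, from Functional and perfusion parameters.
- Cut-off: 95th percentile, two-tailed, 5,000 permutations, from the same section.
- Group sizes: 40 evaluable and 55 enrolled per group, from Subject.
- Assumption for the simulation: normally distributed property values with no group difference.

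**Step 1: can the stated 5% be reproduced?** With equal groups, swapping the labels reverses the sign of the difference, so the permutation distribution is symmetric about zero. If percentile p of the signed distribution is the cut-off in both directions, the size is 2 × (1 − Φ(z_p)).

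- p = 0.95: 2 × (1 − Φ(1.645)) = 2 × 0.05 = 0.10.
- p = 0.975: 2 × (1 − Φ(1.960)) = 2 × 0.025 = 0.05.

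The stated 5% is not reproduced with the 95th percentile used in both directions. It is reproduced with the 97.5th and its mirror image.

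**Step 2: simulation of the permutation test.** 1,000 null data sets were generated at each group size, with 5,000 permutations each. Rejection rates were:

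| Cut-off rule | Expected | 40 per group | 55 per group |
|---|---|---|---|
| Signed 95th percentile, absolute observed difference compared with it | 10% | 10.9% | 10.6% |
| Signed 5th and 95th percentiles | 10% | 10.9% | 10.7% |
| Signed 95th percentile, upper side only | 5% | 4.9% | 5.5% |
| Signed 2.5th and 97.5th percentiles | 5% | 5.5% | 5.1% |
| 95th percentile of the absolute difference | 5% | 5.4% | 5.2% |

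The simulation standard error is √(0.10 × 0.90 / 1000) = 0.9 points for the first two rows and √(0.05 × 0.95 / 1000) = 0.7 points for the others. All results agree with the expected values within that error.

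A second run (2,000 data sets, 2,000 permutations, 40 per group) gave 10.7% for the 5th/95th pair, 5.25% for the upper side only, 5.9% for the 2.5th/97.5th pair and 5.85% for the absolute difference. Its standard errors are about 0.7 points near 10% and 0.5 points near 5%.

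**Step 3: what the choice of cut-off decides.** With 40 per group (78 degrees of freedom), the two cut-offs correspond to about 1.66 and 1.99 standard errors. The standard error of the difference is √(2/40) = 0.224 standard deviations. The cut-offs are therefore 1.66 × 0.224 = 0.37 and 1.99 × 0.224 = 0.45 standard deviations. An observed difference between these values is significant under the literal two-directional reading and not significant in a 5% two-tailed test.

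**The case against.** The best defence is that the sentence is shorthand. The text calls the difference neither signed nor absolute. One percentile of the absolute difference is a usual way to run a two-tailed test, and the plural in the sentence could mean the two limits of the central 95%. Both readings give exactly 5%. The 5% level in Statistical analysis, the two-sided alpha in Subject and the sentence's own sidedness all suggest that a 5% two-tailed test was intended. No 5th/95th pair appears anywhere. The article also cites a method source and condenses a fuller protocol, and either may be clearer.

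Much of this stands. A reader might infer that the true false-positive rate of the topology tests is 10%, twice the stated rate. The document does not support that: the rate depends on what is coded, and the upper-side reading does not double it. A reader might also infer that an upper-side test could not detect lower values in migraine. That would require knowing which group is subtracted from which, and the text does not say.

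The defence does not remove the problem. The intended rule is not on the page, and the written rule does not deliver the stated level. This is not a detail left to another document: the article chose to state the critical value and stated one that conflicts with its own alpha and sidedness.

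The section's closing family-wise corrected threshold does not repair it either. That line follows the sentence on Spearman correlations and is not tied to the permutation cut-off. If it did apply, it would require a stricter per-test cut-off, further from the one stated.

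**Conclusion.** The decision rule is wrong as written and should be corrected. Read literally and applied in both directions, each topology test has a type I error of about 10% instead of 5%. Applied on one side, it has the stated level but is not two-tailed. It meets the plan's claim only under a meaning that the text does not express.

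The 10% figure rests on a signed statistic and a symmetric null distribution. Symmetry is exact with equal groups and approximate otherwise. The arithmetic is certain; which procedure will be run is not.

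The reach is limited to the topological properties, one item among the secondary outcomes. White matter integrity, the grey-matter, ReHo, ALFF and CBF comparisons and the sample size do not use this cut-off. That makes it a should-fix, not a flaw that threatens the trial's main conclusion.

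**What to change.** Replace the sentence with:

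> *The 2.5th and 97.5th percentiles of each permutation distribution of the mean difference will be used as critical values for a two-tailed test at the 5% level.*

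The 95th percentile of the absolute mean difference would do as well. The two rules coincide when the groups are equal in size and nearly coincide otherwise. Because drop-out may leave unequal groups, one of them should be named before the data are analysed.

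The change costs one sentence and, if the literal version has been coded, one line of code. No new data are needed.

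The statistical price, relative to the literal two-directional reading, is the higher critical value. As an illustration, take a true difference of 0.63 standard deviations, an assumed value that gives 80% power with 40 per group under the normal approximation. Here 0.63 × √(40/2) = 2.817, so power falls from Φ(2.817 − 1.645) = 0.88 to Φ(2.817 − 1.960) = 0.80. The power given up was obtained only by testing at 10%. If the authors already meant a 5% rule, nothing is lost.

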### Correlation analysis

Linear regression analysis will be performed across the migraine groups to assess relationships between imaging properties and cognitive testing scores and clinical information. When the most sensitive parameters are found, a receiver operating characteristic (ROC) curve will be plotted to testify the sensitivity and specificity of the certain parameter for quantifying the degree of migraine and screening the accompanied cognitive decline.

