**Discussion:**

Multi-modal imaging features of both healthy controls and perimenopausal women who are susceptible to estrogen decline will be acquired. Imaging features will include volumetric characteristics, white matter integrity, functional characteristics, topological properties, and perfusion properties. Clinical information, such as basic information, blood estrogen level, information of migraine, and a bunch of neurological scale will also be used for statistic assessment. This clinical trial would help to build an effective screen system for quantifying the severity of illness of those susceptible women during the perimenopausal period.

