### Clinical assessments

Demographic and clinical features of all subjects will be collected and recorded, such as age, education level, body mass index (BMI), occupation and menstrual cycle. All participants will receive the following battery of neuropsychological tests: Montreal Cognitive Assessment (MoCA) and Mini-mental State Examination (MMSE) will be used to assess the mental state of subjects. The Short Form health survey (SF-36) will be applied to evaluate the quality of life, and Self-rating Depression Scale (SDS) and Self-rating Anxiety Scale (SAS) will be performed to measure the severity of self-reported depression and anxiety. Migraine will be diagnosed according to the International Headache Society (IHS) criteria of the International Classification of Headache Disorders (ICHD-3 beta version) [1]. The following data will be collected from migraine participants: (1) type of migraine (migraine with aura, migraine without aura, etc.), (2) frequency of migraine attacks, (3) duration of migraine attacks, (4) headache location (unilateral or bilateral), (5) Migraine Disability Assessment Scale (MIDAS) score (the score is divided into 4 grades, higher grade means more severer disability). Blood samples were drawn at the screening centers and processed within 2 h according to a standardized protocol to assess the hormone level [24].

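### The ROC analysis evaluates imaging parameters in the only cohort described, after choosing them there for performance, and names no reference variable or cut-off for migraine severity or cognitive decline

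*Protocol article*

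**What the plan says.** Under Correlation analysis, the protocol article first plans linear regression of imaging properties on cognitive scores and clinical information among the migraine patients. It then says: "When the most sensitive parameters are found, a receiver operating characteristic (ROC) curve will be plotted to testify the sensitivity and specificity". The stated purpose of the curve is "for quantifying the degree of migraine and screening the accompanied cognitive decline". That section names no reference variable, cut-off, validation sample or resampling step.

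The candidate parameters come from the sections on structural parameters and on functional and perfusion parameters: GMV, MK, MD, FA, ReHo, ALFF/fALFF and CBF, each tested by voxel and by region, plus functional connectivity and topological properties. Those sections compare migraine with control and set an FWE-corrected threshold of P < 0.05.

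Possible severity references are collected. Under Clinical assessments these are attack frequency, attack duration and MIDAS ("the score is divided into 4 grades, higher grade means more severer disability"). Under Secondary outcomes measure there is a 1–10 headache VAS. MoCA and MMSE are collected for cognition.

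The Subject section describes one migraine group and one control group: "Considering the drop-out ratio (25%) and unqualified images of included subjects, the total sample size is 55 in each group". The Abstract says the trial would help to "build an effective screen system for quantifying the severity of illness".

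**The concern.** Two problems meet in one sentence of the plan.

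First, a parameter chosen because it performs best in a sample will look better in that sample than in new patients. The cut-point read off the same curve adds to this. The article gives the order of the steps, describes a single cohort and states no correction.

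Second, an ROC curve needs a binary truth. Degree of migraine is graded, and cognitive decline is measured by continuous scales; neither is given a dividing line. With several candidate measures available, the choice can be made after the data are seen. The contrast is open too. The tests that look for imaging differences compare migraine with control, whereas the regression just before the ROC is within migraine patients. A curve against headache-free controls would show presence of migraine, not its severity.

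At stake is the trial's practical claim. The article motivates a severity measure by the wish to avoid overuse of HRT, and this ROC is the only planned analysis that yields sensitivity and specificity in support of it.

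**Working it through.** **The plan's own figure.** The article gives no ROC figure. Its sample size does reproduce: 40 / (1 − 0.25) = 53.3, rounded up to 54, against 55 stated, and the extra woman fits the allowance for unqualified images. No effect size is given for the 40. At two-sided 0.05 and power 0.80, it implies d = √(2/40) × (1.960 + 0.842) = 0.63.

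**Inputs.**
- From the article: 40 analysable women per group; selection before the ROC; at least 8 named global measures (GMV, MK, MD, FA, ReHo, ALFF, fALFF, CBF), more by region.
- Assumed: K = 8 to 50 candidate parameters, normal and independent unless stated; a 20/20 split of 40 migraineurs by severity.

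**Spread of a null AUC.** SD = √[(n1 + n0 + 1) / (12 × n1 × n0)].
- 40 v 40: √[81 / (12 × 1600)] = 0.065.
- 20 v 20: √[41 / (12 × 400)] = 0.092.

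**Best of K, no true signal, no significance gate.** In each simulated data set the parameter with the AUC farthest from 0.50 is picked and its AUC read in the same women. The AUC expected in new patients is 0.50.

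| K | 40 v 40 | 20 v 20 |
|---|---|---|
| 8 | 0.62 | 0.66 |
| 20 | 0.64 | 0.70 |
| 50 | 0.66 | 0.73 |

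The excess agrees with the SD. At 40 v 40 it runs from 0.117 / 0.065 = 1.8 SD (K = 8) to 0.162 / 0.065 = 2.5 SD (K = 50), as expected for the largest of that many absolute deviations. Sensitivity and specificity at the best cut-point, 40 v 40, are about 0.63/0.63 (K = 8) and 0.66/0.66 (K = 50), where 0.50/0.50 is uninformative.

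**Correlated parameters.** With pairwise correlation 0.5, the AUC ranges for K = 8 to 50 fall to 0.61–0.64 (40 v 40) and 0.65–0.70 (20 v 20).

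**With a family-wise gate.** The parameter goes to the ROC only if its two-sample t-test passes Bonferroni at 0.05 (40 v 40, independent parameters, the same effect in each, K = 8 to 50).

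| True d | True AUC | Some parameter passes | Mean apparent AUC of the selected one |
|---|---|---|---|
| 0 | 0.50 | about 5% | 0.69–0.72 |
| 0.3 | 0.58 | 47–68% | 0.70–0.73 |
| 0.626 | 0.67 | over 99% | 0.75–0.80 |

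The gate makes null selection rare. Among parameters that pass, the AUC is still overstated by about 0.08 to 0.13 at d = 0.626 (0.753 − 0.671; 0.798 − 0.671), and by 0.12 to 0.15 at d = 0.3 (0.702 − 0.584; 0.734 − 0.584).

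**The case against.** A condensed article commonly leaves cross-validation and cut-points to the full protocol or analysis plan, and neither is shown. That stands against any claim that a correction is known to be absent: evaluation in the same women is an inference from the single cohort described. It does not dispose of the point, because the article itself fixes the order of selection and evaluation and states the two targets.

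Three stronger readings are tempting, and the article does not support them.

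- A reader might infer that the trial has no severity reference. It collects several; what is missing is the designation of one, with a cut-off, for this curve.
- A reader might infer that the ROC cannot measure severity because it compares migraine with control. The text does not say so. The preceding regression and the stated purpose make a curve within migraineurs at least as natural a reading.
- A reader might infer that a good AUC will emerge even when no parameter is informative. The FWE threshold in the two preceding sections may govern which parameters reach the ROC, and null parameters would then seldom get there. The Correlation analysis section does not state that link, and the gate does not remove overestimation in those that pass.

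The size also depends on K, which the article does not give. Larger pools give larger bias, but the 8 named global measures are the only count the text supports directly.

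Finally, ROC accuracy is neither a primary nor a secondary outcome. The primary outcome, white matter integrity, is unaffected, and the Abstract claims only to help build a screening system.

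**Conclusion.** The concern holds in this form: the ROC is planned on parameters chosen for performance in the only cohort described, with no stated optimism correction, no designated reference or cut-off for either target, and an unclear contrast.

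With no signal and no gate, apparent AUC exceeds the truth on average by about 0.12 to 0.16 at 40 v 40, and by about 0.16 to 0.23 for a 20/20 severity split. These sizes rest on 8 to 50 independent parameters, 40 analysable women per group and an even split; correlation lowers them. A gate changes the nature of the problem from false selection to overestimation of the parameters that pass.

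This should be fixed. It is not critical to the trial, because the outcomes listed do not depend on it.

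**What to change.** - Designate one collected severity measure and its cut-off (for example MIDAS grade or VAS) as the reference for an ROC within the migraine group, and one cognitive scale and cut-off for the second target, before the data are examined.
- Put parameter selection, including any FWE gate, and cut-point choice inside repeated cross-validation or bootstrap optimism correction.
- Report corrected AUC, sensitivity and specificity with 95% confidence intervals beside the apparent values.
- Label any migraine-v-control ROC as exploratory and as showing presence, not severity.

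The cost is more computing and a few sentences of text, with no new patients or scans. The accuracy figures will be lower and their intervals wider.

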## Abstract

**Background:**

As a common clinical symptom that often bothers midlife females, migraine is closely associated with perimenopause. Previous studies suggest that one of the most prominent triggers is the sudden decline of estrogen during perimenopausal period. Hormone replacement therapy (HRT) is widely used to prevent this suffering in perimenopausal women, but effective diagnostic system is lacked for quantifying the severity of the diseaase. To avoid the abuse and overuse of HRT, we propose to conduct a diagnostic trial using multimodal MRI techniques to quantify the severity of these perimenopausal migraineurs who are susceptible to the decline of estrogen.

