In the past two decades, functional magnetic resonance imaging (fMRI) technique has become an indispensable tool in migraine research and has greatly contributed to our understanding of migraine pathophysiology [15–17]. It could show anatomic and functional cerebral transformations associated with the clinical evolution and could be applied to most individuals without adverse effects. Maleki et al. found that female migraineurs have thicker posterior insula and precuneus cortices as compared with both male migraineurs and healthy controls of both sexes [18]. Compared to healthy controls, Kim and colleagues revealed a reduction of gray matter (GM) density in migraineurs, including insula, motor/premotor, prefrontal, cingulate, posterior parietal, and orbitofrontal cortex [19]. Huang et al. found reduced fractional anisotropy (FA) in the right frontal of migraine patients by using a tract-based spatial statistics (TBSS) method, which means the microstructure of white matter (WM) in that region is impaired [20]. Liu et al. found that the resting-state functional connectivity (FC) was disrupted in patients with long-term migraine through the method of graph theory [21]. However, these researches are all focused on both male and female patients at all ages, which contributes little to quantify the degree of migraine in perimenopausal women. According to our knowledge, no previous studies had researched the imaging abnormality of perimenopausal women who are susceptible to the decline of estrogen. Since estrogen plays a pivotal role in pain transmission in our brain [10], we thus raised the current hypothesis that brain structure and function of these women who are susceptible to estrogen drop exhibit unique characteristic changes in multi-modal images.

Consequently, we would like to conduct a prospective clinical trial to investigate the imaging abnormalities in these susceptible perimenopausal women. At the beginning, perimenopausal women around who had migraine will be recruited from the pain clinic of our hospital. Perimenopausal women around who did not have migraine will be recruited as healthy controls (HC) from the local community. Then, these subjects will undergo a series of multi-modal MRI brain scans and neuropsychology scales to assess the mental and physical state of these subjects. Multi-modal MR images of these two groups of subjects will be compared to find significant features as objective biomarkers.

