#### Structural parameters

Both voxel-based and ROI-based 2-sample Student-t test will be applied to compare global gray matter (GMV) MK, MD and FA between susceptible group and healthy control group with age, sex, education and BMI as covariance. Moreover, non-parametric Spearman correlation will be performed to delineate a possible relationship between local morphologic alterations and clinical data as well as diffusional alterations and clinical data. Significance threshold, which is corrected for comparison using Family Wise Error (FWE) method, will be set at *P* < 0.05. For each design matrix, significant effects both in the negative and positive directions are considered.

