## Discussion

Multi-modal imaging features of perimenopausal women who are susceptible to estrogen decline will be acquired. Imaging sequences will include 3D-BRAVO, DKI, RS-BOLD and 3D-pCASL. Imaging features for assessment will include volumetric characteristics, white matter integrity, functional characteristics, topological properties and perfusion properties. Clinical information, such as information of migraine, headache level, MIDAS score, SAS, SDS, MMSE, MoCA and SF-36 will also be acquired for assessment.

The structural imaging could reflect the long-term impact of migraine on the brain structure, including GM volume and WM integrity. VBM has been pervasively used to investigate structural changes in migraine in the last decade. Some of them observed significant GM abnormalities in several brain regions of migraine patients [30–32], including right superior temporal gyrus, right inferior frontal gyrus and left precentral gyrus etc., but the result in other studies were not significant [33–35]. Two recent meta-analysis considered that migraine could cause GMV changes, and these changes were related to gender [36]. The integrity of WM is usually measured by calculating several parameters of its diffusional ability, such as MD, MK and FA. Several previous studies had compared these parameters between migraine patients and healthy controls, and they found significant increases or decreases in brain regions like thalami, corpus callosum and internal capsule [37–40]. Previous studies had also investigated the difference of WM integrity between migraine patients with and without aura and between ictal and interictal period [37, 41]. In addition, imaging researches about WM integrity in children or adolescent who have migraine had also been conducted [42, 43]. In the current study, we hope that the long-term impact of the susceptibility of estrogen drop on brain structure could also be reflected in structural imaging.

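### The aim is to grade severity with multimodal MRI, but the only accuracy analysis is a ROC for one parameter, picked and evaluated on the same women

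*Protocol article*

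**What the plan says.** All places are in the protocol article.

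- **Aim.** The abstract's Background proposes "a diagnostic trial using multimodal MRI techniques to quantify the severity of these perimenopausal migraineurs". The abstract's Discussion adds: "This clinical trial would help to build an effective screen system for quantifying the severity of illness". The main Background gives the working step: "Multi-modal MR images of these two groups of subjects will be compared to find significant features as objective biomarkers".
- **Acquisition.** Four sequences are taken per woman (Discussion: "Imaging sequences will include 3D-BRAVO, DKI, RS-BOLD and 3D-pCASL"). They yield five feature types: volumetric, white matter, functional, topological and perfusion.
- **Group tests.** Structural parameters: "Both voxel-based and ROI-based 2-sample Student-t test will be applied to compare global gray matter (GMV) MK, MD and FA". Functional and perfusion parameters: "Both voxel-based and ROI-based 2-sample Student-t test will be applied to compare global ReHo, ALFF/fALFF, CBF". Topological properties are compared one at a time by permutation.
- **Severity and accuracy.** Correlation analysis states a linear regression of imaging properties on cognitive scores and clinical information in the migraine women. It then states a ROC curve, once the most sensitive parameters are known, for the "sensitivity and specificity of the certain parameter for quantifying the degree of migraine" and for detecting cognitive decline.

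**The concern.** The purpose is multimodal and concerns severity, but the accuracy analysis rests on one parameter. Two things follow.

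1. No stated result compares the modalities together with the best of them alone. If single parameters grade severity poorly, the trial could report that MRI does so, although the combination was never assessed.
2. The article describes one cohort and no resampling. A parameter chosen because it did best in that cohort, and then given a ROC curve in it, will look better than it would in new patients.

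The aim and the analysis are both written down and do not match. This is more than detail that a condensed article leaves out.

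**Working it through.** **Structure**

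| Step | Section | Unit of analysis |
|---|---|---|
| t-tests on GMV, MK, MD, FA | Structural parameters | one measure at a time |
| t-tests on ReHo, ALFF/fALFF, CBF | Functional and perfusion parameters | one measure at a time |
| Permutation tests | same | one topological property at a time |
| Linear regression | Correlation analysis | not stated: single or several predictors |
| ROC | Correlation analysis | one parameter, or several curves of one parameter each |

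No row carries a combined score into an accuracy measure.

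**The plan's own figures**

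The Subject section gives 40 per group, power 0.80, two-sided 0.05, 25% drop-out and 55 per group. 40/0.75 = 53.3, rounded up to 54. The stated 55 fits once unusable images are allowed for. No effect size is given, so solving the two-sample t-test backwards for n = 40 gives d = 0.634. This is the detectable difference, not an expected one.

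**One parameter**

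AUC = Φ(d/√2) = Φ(0.634/1.414) = 0.67, for migraine versus control.

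**Five parameters together (population values)**

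Assume one per feature type, each with d = 0.634 and common correlation c. Then D = d√(5/(1+4c)) and AUC = Φ(D/√2):

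- c = 0: D = 0.634 × 2.236 = 1.418, AUC 0.84
- c = 0.3: D = 0.634 × 1.508 = 0.956, AUC 0.75
- c = 0.5: D = 0.634 × 1.291 = 0.819, AUC 0.72

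**After cross-validation** (simulation, 40 v 40, stratified 10-fold, fixed-penalty ridge; single parameter chosen inside the folds)

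| Assumed effects | Combined AUC | Best single AUC |
|---|---|---|
| Five equal, c = 0 | 0.83 | 0.67 |
| Five equal, c = 0.3 | 0.73 | 0.67 |
| Five equal, c = 0.5 | 0.69 | 0.67 |
| One informative, four null, c = 0 | 0.63 | 0.65 |

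**Severity as a continuous score**

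Assume five parameters each correlating 0.3 with severity. Population R² = 5 × 0.09/(1+4c) = 0.32, 0.20 and 0.15 for c = 0.1, 0.3 and 0.5, against 0.09 for one. In nested cross-validation with 40 women, the combined figures fall to about 0.21, 0.11 and 0.09.

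**Optimism of selecting and testing on the same data**

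With no true signal and either direction allowed, the mean apparent AUC of the best parameter at 40 v 40 is 0.55 for one candidate, about 0.60 for five and 0.62 for eight. If the 40 migraine women were split 20 v 20 by severity (an assumption), it is 0.66 for the best of eight. The true value is 0.50 throughout.

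**The case against.** The strongest reply is that multimodal describes the acquisition, and that the trial is a biomarker search that comes before any combined tool. The abstract says only that the trial would help towards a screening system, the main Background speaks of finding features, and the primary outcome is one feature type, white matter integrity. Screening features singly first is a legitimate order of work.

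Much of this stands, and it rules out several stronger readings:

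- A reader might infer that every parameter is analysed alone. That is certain for the group tests and for the ROC as worded. It is not established for the regression, which could enter several imaging properties.
- A reader might infer that the trial promises a finished multimodal system and cannot deliver it. The wording is softer than that.
- A reader might infer that combining would surely do better, so the single-parameter ROC should be replaced. The large gain needs five equal, weakly correlated effects. The article's Discussion itself cites non-significant grey matter studies and one ASL study without significant changes. With one informative parameter the combination gains nothing.
- The AUC figures above concern migraine versus control, whereas the planned ROC concerns the degree of migraine. They show the range of possible gain, not a forecast for severity.

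The reply does not explain why the accuracy analysis, which the article does specify, stops at one parameter when the announced purpose is to quantify severity with several modalities. It also does not touch the optimism from selecting and evaluating on the same data.

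**Conclusion.** The mismatch holds: the stated aim is multimodal grading of severity, and the only accuracy analysis is a single-parameter ROC on the data used for selection. The plan therefore cannot show whether the modalities together do better than one. Its ROC would also be optimistic, by about 0.10 in AUC (0.60 against 0.50) for the best of five uninformative parameters at 40 v 40.

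What combining would add is uncertain. Cross-validated, it runs from 0.16 in AUC (0.83 v 0.67) to slightly negative (0.63 v 0.65). These figures rest on assumed effects and correlations, because the article gives none. The between-group comparisons are not affected. The change should be made, as an addition to the planned ROC rather than a replacement.

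**What to change.** Under Correlation analysis:

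1. Keep the single-parameter ROC, but choose the parameter inside 10-fold cross-validation and report its cross-validated AUC.
2. Add one pre-specified penalised regression with one summary per feature type fixed in advance, for example mean MK, GMV, ReHo, global network efficiency and CBF. Choose the penalty inside the folds.
3. Fit it in the migraine group against one named severity measure already collected, for example the MIDAS score. State in advance a split of the four MIDAS grades for the AUC.
4. Report cross-validated R² and AUC for the combined model beside those of the best single parameter, without presuming which wins.
5. State whether the existing linear regression is multivariable.

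If no combined model is wanted, reword the aim in the abstract as a search for single imaging biomarkers.

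The cost is analysis wording and modest programming; no extra women or scans are needed. The summaries must be fixed in advance, which gives up some regional detail in this one model, and the accuracy figures will look less favourable than an apparent ROC.
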